### Outcome measures

#### Pain intensity

The primary outcome will be the visual analog scale (VAS) score to measure pain with motion. To assess the perception of DOMS after the treadmill exercise, four separate baseline pain intensity measures will be recorded: the NRS score, a VAS with motion, a VAS at rest, and a VAS after walking downstairs. Pain intensity will be measured before the exercise, immediately after the exercise, and 1, 6, 12, 24, 36, 48, 60, and 72 h after the exercise.

The VAS is one of the most widely used measures of pain intensity, determined on a 100-mm horizontal line, where 0 indicates “no pain” and 100 indicates “the worst imaginable pain” [32, 33]. Assessors will record the length of the point marked by the subject. For the NRS pain score, the subjects will be asked to report overall pain intensity on a single 11-point numeric scale, with 0 indicating “no pain” and 10 representing “the worst imaginable pain” [33]. Although studies have shown that both the VAS and NRS have similar sensitivity in pain assessments, the VAS is believed to have a higher degree of precision [34, 35]. However, the NRS has the advantage that it can be used effectively across all types of disorders because it is easy and simple. To take advantage of each method, the VAS will be used to evaluate the detailed pain intensity with motion, whereas the NRS will be used to evaluate the overall pain intensity.

To assess time-weighted overall pain intensity, the sum of the pain intensity differences (SPID), which is an outcome measure that summarizes the treatment response over a period of time, will be calculated using the NRS scores that were evaluated before exercise and at 24, 48, and 72 h after exercise [36]. The SPID_72_ value will be obtained according to the following calculation: (1) PID (pain intensity difference) = NRS_t_ – NRS_baseline_; (2) SPID_t_ = ∑PID_t_ * (time in hours elapsed since the previous observation). A higher SPID_72_ value indicates larger differences in pain intensity over the 72 h after exercise.

#### Calf circumference

The circumference around both legs will be measured at the level of acupuncture point BL57, horizontally on the ground to obtain a constant reference point. BL57 is in the middle of the calf between the two heads of the gastrocnemius muscle. After marking the acupuncture point with a pen for repeatability, the same measurer will use the same tape to repeat the measurements. The average value will be calculated after measuring three times consecutively. Calf circumferences will be measured before the exercise, immediately after the exercise, and 1, 6, 12, 24, 36, 48, 60, and 72 h after the exercise.

#### Pain threshold

Pain threshold will be measured using a digital algometer (model FPX25, Wagner Instruments, Greenwich, CT, USA). The point of measurement will be acupuncture point BL57 in both calves, at which the rubber tip will be pressed perpendicularly into the muscle with a consistently increasing force of 0.25 kg/cm^2^/s [37]. The values will be obtained when the subject indicates the onset of pain. Each leg will be measured three times after brief resetting times. Average values will be obtained for further analysis. The pain threshold will be measured immediately after measuring the calf circumference.

#### Muscle damage and inflammation

Venous blood samples will be collected to assess muscle damage and inflammation. Plasma CK activity will be used to assess muscle damage. C-reactive protein (CRP) and interleukin-6 (IL-6) concentrations will be measured to evaluate the inflammation induced by eccentric exercise. Whole blood samples will be obtained and centrifuged to isolate the serum. The samples will be stored at − 80 °C and analyzed at the end of the study. As plasma concentrations of the markers will differ depending on the reaction time, each marker will be collected at the appropriate time [38, 39]. Blood samples for CK activity will be collected at six different time points: before exercise, and 12, 24, 48, 60, and 72 h after the exercise. Blood samples for the inflammation markers will be collected at six different time points, including before the exercise, immediately after the exercise, and 1, 6, 12, and 24 h after the exercise.

#### Safety assessment

Blood pressure and heart rate will be measured every day using an automated device. In addition, blood tests will be conducted before and after the drug intervention during each hospitalization. The blood tests will include aspartate aminotransferase, alanine aminotransferase, alkaline phosphatase, total bilirubin, gamma-glutamyl transpeptidase, protein, albumin, blood urea nitrogen, creatinine, red blood cells, hematocrit, hemoglobin, white blood cells, and lipids.

### Exploratory outcomes

#### Metabolomics analysis

During the hospitalization, plasma and urine samples will be obtained three times (before the exercise, 1 h after the exercise, and 72 h after the exercise) to examine the drug-induced and exercise-induced changes in metabolites. Urine samples and plasma will be aliquoted into empty vials and maintained at − 80 °C until further analysis. When the trial has been completed, all samples will be analyzed simultaneously. Non-targeted analysis by mass spectrometry will be used to determine the metabolic changes after exercise and the drug intervention; this evaluation is called “sportomics” [11–13]. Briefly, the supernatants will be obtained by adding acetonitrile or methanol, and the solution will be injected into an ultra-performance liquid chromatography/quadrupole time-of-flight mass spectrometry (UPLC-Q/TOF-MS, Synapt G2Si; Waters, Milford, MA, USA) system. Information from the mass data, including retention time, ion intensity, and m/z will be extracted. After alignment and normalization, the multivariate data matrix will be exported into SIMCA-P (Umetrics, Umea, Sweden) for a multivariate statistical analysis. The ions contributing to separation of the JGT and placebo groups will be further investigated by searching the METLIN and human metabolomics databases.

#### Other outcomes

The degree of pain induced by eccentric exercise can vary depending on the usual momentum and body composition. To determine the effects of usual physical activity and body composition on DOMS symptoms, the Korean version of the International Physical Activity Questionnaire-Short Form (IPAQ-SF) and a body composition analysis will be performed on the first day of hospitalization. The IPAQ-SF consists of seven questions asking about the amount of time spent per week on activities (walking as well as moderate and vigorous activities) and sitting [11, 12]. The total weekly physical activity for each activity category will be estimated by a metabolic equivalent energy expenditure [11]. Body composition parameters, such as body fat percentage, fat mass, and muscle mass will be obtained with the InBody 720 instrument (Biospace, Seoul, Republic of Korea).

### Sample size

As no clinical trial has evaluated the efficacy of JGT on DOMS, a sample size calculation was impossible. A study estimating the sample size for a pilot study proposed 15 subjects per treatment arm as an optimal sample size for the standardized effect size with 90% power and two-sided 5% significance [8].

### Statistical analysis

The statistical analysis will be conducted by an independent statistician using SAS version 9.4 (SAS Institute). The significance level will be set at 0.05 in a two-tailed test. All continuous data will be presented as means and 95% confidence intervals (CIs). Categorical data will be reported as frequencies and percentages. The intention-to-treat (ITT) principle will be applied for the primary analysis. The ITT population will include subjects who meet the full analysis set (FAS) criteria, including subjects who had the primary outcomes assessed once or more except for the baseline measures and who took the test drug at least once. Subjects who do not meet the eligibility criteria, those who did not take the test drug throughout the study, and those who have never been evaluated after the screening visit will be excluded from the FAS dataset. The per-protocol set will also be analyzed, which will only include subjects who have completed the study as a supplementary analysis.

The baseline characteristics of the study subjects will be presented using a descriptive analysis for each group. The primary outcome will be the differences between the VAS score with motion measured at various intervals from 0 to 72 h after exercise. A mixed-effect model for repeated measures (MMRM) will be used to assess differences along with the time effect. The dependent variable will be the change in the VAS score (pain with motion) measured from 0 to 72 h after exercise. The model will include treatment and protocol-specified visits as fixed effects, and subjects as a random factor. Dunnett’s test will be used for multiple comparisons. The results of the secondary effective analysis will be analyzed using the same method as for the primary outcome, in the case of continuous variables with time variation. Additionally, Student’s *t* test or Wilcoxon’s signed-rank test will be used to compare results before and after the treatment within each group. Categorical data will be analyzed using the chi-squared test or Fisher’s exact test. Missing values by maximum likelihood will be considered when the MMRM is used. The last observation carried forward method will be adopted for missing values for Student’s paired *t* test, the Wilcoxon signed-rank test, or repeated measures analysis of variance.

The incidence of serious adverse events (SAEs) and adverse events (AEs) related to the treatment will be analyzed for the safety assessment using the independent *t* test or Wilcoxon’s rank-sum test. The percentage of subjects who experienced one or more side effects during the study will be analyzed using Pearson’s chi-squared test or Fisher’s exact test.

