## Methods and design

### Objective

The aim of this study is to assess the therapeutic effect of JGT in the relief of DOMS symptoms. The primary outcome is the difference between the JGT and placebo groups in pain intensity, measured every 12 h from 0 to 72 h after exercise. Our secondary outcomes include the pain threshold in the calf muscles, calf circumference, and serum markers of muscle damage. Furthermore, exercise-induced shifts in serum and urinary metabolites will be analyzed using a metabolomics-based analysis.

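### The primary model analyses a change in VAS with no named reference time and no baseline term; name the pre-exercise value and adjust for it

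*Protocol article*

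**What the plan says.** The Pain intensity section names the primary measure: "The primary outcome will be the visual analog scale (VAS) score to measure pain with motion". The Objective section describes it as a difference between treatments in pain intensity. The Statistical analysis section then sets the response of the mixed model for repeated measures: "The dependent variable will be the change in the VAS score (pain with motion) measured from 0 to 72 h after exercise". The terms follow: "The model will include treatment and protocol-specified visits as fixed effects, and subjects as a random factor". Continuous secondary outcomes that vary over time are to be analysed in the same way.

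Two readings in each stay could serve as the reference: "Pain intensity will be measured before the exercise, immediately after the exercise, and 1, 6, 12, 24, 36, 48, 60, and 72 h". In Table 1 the pre-exercise (-1 h) and 0 h readings both come before the first dose at 1 h. The only baseline subtraction that is spelled out is the one for SPID, which uses NRS scores "evaluated before exercise and at 24, 48, and 72 h after exercise", so its reference is pre-exercise. No equivalent statement is made for the VAS, pain threshold or calf circumference.

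**The concern.** Two things are left in a poor state. First, the primary response is a change from an unnamed time. Change from a rested state and change from the acute post-exercise state are different quantities with different variances, and the choice between them should not be open once data are in hand.

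Second, the stated model subtracts the baseline but does not adjust for it. In a 2 x 2 crossover the subject effect already removes stable differences between men. What a same-stay baseline adds is information on how this stay differs from the other one. Subtraction assumes that a one-unit difference in baseline between stays carries through to a one-unit difference in outcome. Where the true slope is smaller, subtraction brings in baseline noise. A covariate lets the data set the slope.

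At stake is precision, and with it power in a trial of 30 men. Because treatment order is randomised, neither the score nor the change is biased on this account.

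**Working it through.** **The plan's own figure.** There is none to reproduce. The Sample size section says a calculation was impossible and cites 15 per arm at 90% power without an effect size, SD or correlation. The comparison below is therefore conditional on assumed values.

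**Inputs from the article.** 30 subjects, each receiving both treatments; two-sided 5% level.

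**Assumptions.** All 30 complete. Work with each subject's between-stay difference. Let k be the SD of the baseline difference divided by the SD of the outcome difference, and rho the correlation of the two. The true effect is set so that the raw score has 80% power with 28 df. That is 0.530 SD of the outcome difference, or a noncentrality of 0.530 x sqrt(30) = 2.90.

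**Formulas (variance relative to the raw score).**
- Unadjusted change: 1 + k² - 2·rho·k, 28 df.
- Baseline as covariate: 1 - rho², 27 df.
- Power from the noncentral t, with the noncentrality divided by the square root of the relative variance.

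Example, k = 1 and rho = 0. Change: 1 + 1 - 0 = 2, SE ratio 1.41, noncentrality 2.90/1.41 = 2.05, power 51%. Adjusted: 1 - 0 = 1, noncentrality 2.90 on 27 df, power 80%.

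| k | rho | Relative variance, change | Relative variance, adjusted | Power, change | Power, adjusted |
|---|---|---|---|---|---|
| 0.1 | 0 | 1.01 | 1.00 | 79.6% | 79.9% |
| 0.2 | 0 | 1.04 | 1.00 | 78.4% | 79.9% |
| 0.1 | 0.3 | 0.95 | 0.91 | 82.0% | 83.5% |
| 0.5 | 0 | 1.25 | 1.00 | 70.8% | 79.9% |
| 0.5 | 0.5 | 0.75 | 0.75 | 89.9% | 89.8% |
| 1 | 0 | 2.00 | 1.00 | 50.9% | 79.9% |
| 1 | 0.25 | 1.50 | 0.94 | 62.9% | 82.4% |
| 1 | 0.5 | 1.00 | 0.75 | 80.0% | 89.8% |
| 1 | 0.7 | 0.60 | 0.51 | 95.1% | 97.5% |

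**Reading the table.** Change is less precise than the raw score when rho is below k/2 and more precise above it. Adjustment matches or beats change throughout, with a largest shortfall of 0.1 point (k = 0.5, rho = 0.5). The formula charges the covariate only for one degree of freedom. Simulation at k = 1 and rho = 0, which also pays for estimating the slope, gave 79% adjusted against 52% for change, so the real price of an uninformative covariate is about 1 to 1.5 points.

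**Where this trial is likely to sit.** For VAS from pre-exercise, the Background says soreness resolves within 7 days, the wash-out exceeds 1 week and the men are healthy. Pre-exercise VAS should be near zero in both stays, so k is small (0.1 to 0.2, say). At rho 0 to 0.3 the difference is then about 0.3 to 1.5 points. For VAS from 0 h, k could be much larger. Pre-exercise pain threshold and calf circumference are not near a floor, so k could approach 1, but rho is unknown.

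**The case against.** A reader might infer that the article contradicts itself by naming a score in one section and a change in another. That does not hold up well: the Pain intensity section names the instrument and the Statistical analysis section names the metric, which is ordinary in a condensed article. Once the baseline is a linear covariate, score and change give the same treatment estimate, because only the baseline coefficient shifts, by 1.

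A reader might also take the wording of the dependent variable to mean change from 0 h, and conclude that the primary analysis loses a large share of its power. The documents do not support this. The same 0 to 72 h phrase serves elsewhere as a description of the measurement window, in the Background and in the Objective: "The primary outcome is the difference between the JGT and placebo groups in pain intensity, measured every 12 h from 0 to 72 h". If 0 h were the reference, the first visit in the window would be zero for everyone. The one baseline that is defined, for SPID, is pre-exercise.

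Nor can a loss be asserted for pain threshold and calf circumference. Calf circumference is averaged over three readings by the same measurer at a pen mark. If that mark is redrawn for the second stay, which the article does not say, placement error would be shared within a stay and rho could be high enough for subtraction to help.

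Finally, baseline definitions are often left to a full protocol or SAP. That excuses brevity, but this article does fix the response as a change and does list the model terms. The unnamed reference and the missing baseline term therefore stand.

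**Conclusion.** The point holds as a matter of definition and efficiency. The reference time of the primary change is not named, and the listed model subtracts a same-stay baseline with weight 1 where it could adjust for it. On the pre-exercise reading, which the text favours, the cost to the primary VAS is probably a point or two of power at most when rho is low. For pain threshold and calf circumference it ranges from nothing to about 29 points (80% - 51%, at k = 1, rho 0). These sizes rest on assumed k and rho and on 30 completers; the article supplies no SD or correlation. The change is worth making because it is nearly free and closes a choice that would otherwise be open after the data are seen, not because a large loss has been shown.

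**What to change.** In the Statistical analysis section:

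- State that baseline is the pre-exercise (-1 h) value of the same stay, for VAS with motion, pain threshold and calf circumference.
- Add that baseline to the model as fixed covariates in two parts: the subject's mean over both stays, and the stay's deviation from that mean. The deviation is the part that adjusts the within-subject treatment comparison; a single term would mix between-subject and within-subject slopes.
- Use either score or change as the response and say which.
- Do not subtract the 0 h VAS, and do not use it as a covariate while 0 h remains one of the outcome times.

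The cost is a few sentences and one or two degrees of freedom, about 1 to 1.5 points of power if baseline proves uninformative. No new data are needed.

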**Fig. 2 Fig2:**
[figure not shown]
Schedule of enrollment, interventions, and assessments, according to the SPIRIT 2013 statement

**Table 1 Tab1:** Time schedule for the in-hospital clinical trial

Day	Day 1				Day 2				Day 3			Day 4			
Time points	15:00	17:00	18:00	19:00	00:00	6:00	12:00	18:00	6:00	12:00	18:00	6:00	12:00	18:00	19:00
Time after exercise		–1 h	0 h	1 h	6 h	12 h	18 h	24 h	36 h	42 h	48 h	60 h	66 h	72 h	
Blood pressure		○		○		○		○	○		○	○		○	
Check for adverse events				○		○		○	○		○	○		○	
Physical examination	○														
Body composition analysis	◎														
IPAQ-SF questionnaire	◎														
Treadmill exercise			○												
Medication				○		○	○	○	○	○	○	○	○		
Randomization			○												
Blood tests		○												○	
Serum CK analysis		○				○		○			○	○		○	
Serum CRP, IL-6		○	○	○	○	○		○							
Pain intensity assessments		○	○	○	○	○		○	○		○	○		○	
Calf circumferences		○	○	○	○	○		○	○		○	○		○	
Pain threshold		○	○	○	○	○		○	○		○	○		○	
Serum & urine collection		○		○										○	
Blind assessment															○

◎ Assess only at the first hospitalization (Phase I)

*IPAQ-SF* International Physical Activity Questionnaire-Short Form, *CK* creatine kinase, *CRP* C-reactive protein, *IL-6* interleukin-6

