### Intervention

After the treadmill exercise, the subjects will be administered either JGT or the placebo drug three times daily before meals for 3 days (nine times in total). Both the JGT and placebo drug will be manufactured by Kyungjin Pharmaceutical Co., Ltd. (Gyeonggi-do, Republic of Korea) according to Good Manufacturing Practice guidelines. Both drugs will be prepared in the form of light brown granules. The constituents of each drug are shown in Table 2. After the first hospitalization, subjects will be readmitted to the hospital after the wash-out period of more than 1 week. During the second hospitalization, subjects will be administered the other drug, not the one they have taken before, in accordance with the crossover design. No over-the-counter drugs or prescription-based medicines will be permitted throughout the clinical trial. If a subject already has taken a medication during the trial or the subject is suffering from a medical condition that requires medication, the subject will be dropped from the trial.

**Table 2 Tab2:** Constituents of Jakyakgamcho-tang and the placebo control drug

Test drug	Constituents	Contents	Purpose of use
Jackyakgamcho-tang (JGT)		The amount contained in a single dose (3.0 g)	
	*Paeonia lactiflora* Pallas	2 g	Main components (used as a solid extract 480 mg)
	*Glycyrrhiza uralensis* Fischer	2 g	
	Lactose	1650 mg	Excipient
	Cornstarch	720 mg	Excipient
	Colloidal silicon dioxide	150 mg	Excipient
Placebo		The amount contained in a single dose (3.0 g)	
	Lactose	1800 mg	Excipient
	Cornstarch	785 mg	Excipient
	Colloidal silicon dioxide	160 mg	Excipient
	Caramel color	255 mg	Coloring

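### The primary 0–72 h window takes in a pre-dose pain score, its visit list conflicts between sections, and the reference for change is not named, so the treatment main effect is 0.78 to 1.00 of a constant post-dose effect depending on the reading

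*Protocol article*

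**What the plan says.** The protocol article describes the primary outcome in three sections.

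- **Objective:** the JGT–placebo difference in pain intensity, "measured every 12 h from 0 to 72 h after exercise". That is 0, 12, 24, 36, 48, 60 and 72 h.
- **Outcome measures, Pain intensity:** VAS with motion is primary, and pain is "measured before the exercise, immediately after the exercise, and 1, 6, 12, 24, 36, 48, 60, and 72 h after the exercise". Table 1 agrees with this schedule.
- **Statistical analysis:** "The primary outcome will be the differences between the VAS score with motion measured at various intervals from 0 to 72 h after exercise". The dependent variable is then given: "The dependent variable will be the change in the VAS score (pain with motion) measured from 0 to 72 h after exercise". The reference time for the change is not named.

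The model is also given there: "The model will include treatment and protocol-specified visits as fixed effects, and subjects as a random factor". No treatment-by-visit term is listed.

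On timing, the Intervention section says "After the treadmill exercise, the subjects will be administered either JGT or the placebo drug three times daily before meals for 3 days". Table 1 puts the exercise and randomization in the 18:00 / 0 h column. The first medication mark is in the 19:00 / 1 h column, which also holds the 1 h pain assessment.

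**The concern.** A score taken before any drug has been given has an expected treatment difference of zero. If it is averaged into the treatment effect, it pulls the estimate toward zero. The 0 h score is such a score on every reading of the schedule. It is also informative in another way: taken after the bout and before the drug, it shows how hard that bout hit that subject in that hospitalization. That makes it more useful as a covariate than as an outcome.

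The sections also disagree on which visits form the primary outcome, and the change has no stated reference. Two analysts following the text could therefore estimate different quantities, and the choice would still be open when the data are in hand.

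**Working it through.** **The plan's own figures.** The article gives no expected effect, SD or between-visit correlation for VAS. The Sample size section says a calculation was impossible and cites 15 per arm from a pilot-study rule. There is therefore no stated effect or power for this endpoint to reproduce. The schedule itself can be checked.

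**Step 1: the schedule in Table 1.** Pain is marked at −1, 0, 1, 6, 12, 24, 36, 48, 60 and 72 h. That is ten assessments, nine of them after exercise, and it matches Outcome measures. Medication is marked at 1, 12, 18, 24, 36, 42, 48, 60 and 66 h, which matches the nine administrations in the Intervention section. So 0 h is pre-dose, 1 h coincides with the first dose, and 6 h is five hours after it.

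**Step 2: what the model estimates.** With treatment and visit fixed, subject random, no interaction and complete data, the treatment coefficient is the unweighted mean of the K visit-specific differences. Suppose the effect is d at every visit after the first dose and zero at 0 h and 1 h. Then

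estimate = d × (number of post-dose visits) / K.

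| Visits | Reference for change | K | Post-dose visits | Estimate |
|---|---|---|---|---|
| Full schedule | pre-exercise | 9 | 7 | 7/9 = 0.78d |
| 12-hourly | pre-exercise | 7 | 6 | 6/7 = 0.86d |
| Full schedule | 0 h | 8 | 7 | 7/8 = 0.875d |
| 12-hourly | 0 h | 6 | 6 | 6/6 = 1.00d |

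If 0 h is the reference it is no longer an outcome visit, hence K of 8 and 6. If the 1 h score were shown to be post-dose and to carry the full effect, the two full-schedule rows would become 8/9 = 0.89d and 8/8 = 1.00d.

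Simulated mixed models with d = −10 mm (40 runs per row) gave −8.0, −8.5, −8.6 and −10.0, with a Monte Carlo standard error of about 0.2. This is consistent with the table.

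**Step 3: a different time course.** The Background says symptoms usually occur 12–48 h after exercise. If the effect exists only at 12, 24, 36 and 48 h, the four rows become 4/9 = 0.44d, 4/7 = 0.57d, 4/8 = 0.50d and 4/6 = 0.67d. A 12–72 h window then gives 4/6 = 0.67d and a 6–72 h window 4/7 = 0.57d.

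**Step 4: power, as illustration only.** Assumptions not in the document: 30 subjects, noncentral t with 28 df, two-sided 5%, a true effect of 0.5 SD of the visit-level paired difference at post-dose visits, and correlation r between visit-level differences. With equal SDs, the variance of the mean of K differences is (1 + (K − 1)r)/K in units of that SD squared. With SDs s_i it is [Σs_i² + r·Σ_{i≠j} s_i s_j]/K².

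| Window | r = 0.5 | r = 0.7 |
|---|---|---|
| Nine scores, 0 h and 1 h null, equal SD | 79% | 67% |
| Nine scores, SD at 0 h and 1 h half of later | 87% | 77% |
| Nine scores, SD at 0 h and 1 h a quarter of later | 91% | 82% |
| 12-hourly including 0 h, equal SD | 85% | 75% |
| 12–72 h | 93% | 86% |
| 6–72 h | 94% | 87% |

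The loss against 12–72 h on nine scores runs from 93 − 91 = 2 points to 86 − 67 = 19 points, depending on values the document does not give.

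**The case against.** The strongest reply is that dilution is not established. The dependent variable is a change, and the text permits 0 h as its reference. On the 12-hourly grid that removes the dilution entirely. This stands, and it is why the size must be given as a range. Pre-exercise is the likelier reference, because the SPID baseline in Outcome measures is the pre-exercise score, but that is an analogy.

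The decisive contrast is not named either. Assessing differences along with time and listing Dunnett's test suggest visit-wise comparisons, which pre-dose visits would not dilute. That also stands in part, but the listed model has no interaction term to produce them. Interaction and contrast details may sit in an unseen analysis plan; the conflict between the visit lists is in the article itself.

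Four stronger readings are tempting and are not supported:

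- **Three conflicting definitions.** There are three wordings but only two conflicting grids. The Statistical analysis wording is vague and compatible with the full schedule.
- **A certain 22% loss.** The 1 h score is not on the Objective's grid, and Table 1 gives no order of dose and assessment within that column.
- **A known loss of power.** It depends on assumed correlations and early-visit SDs. Early scores may vary less, which shrinks the loss.
- **A need to drop 6 h.** That score is post-dose by Table 1, so the pre-dose argument does not exclude it.

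**Conclusion.** The point holds as a should-fix. Two things are certain from the text: the 0–72 h window includes a pre-dose score, and the Objective's seven-score grid contradicts the nine post-exercise scores in Outcome measures and Table 1. The missing reference for change adds to the ambiguity.

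Under the listed model, a constant post-dose effect and no effect at 0 h or 1 h, the main effect lies between 0.78d and 1.00d, a dilution of 0% to 22%. On the likelier pre-exercise reference it is 14% (12-hourly) or 22% (full schedule). These factors assume complete data and equal visit weights; another covariance structure would change the weights.

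The bias is toward no effect. It does not inflate type I error for a window fixed in advance, although choosing the window after seeing the data could. The document states no effect-size target, so no stated power claim is broken.

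**What to change.** 1. Use one list of post-dose analysis visits in the Objective, Outcome measures and Statistical analysis: either 12–72 h, which keeps the Objective's 12-hourly spacing, or 6–72 h.
2. Remove 0 h as an outcome visit, and 1 h as well unless the documented order shows it to be post-dose. State that order in Table 1. Report excluded early scores descriptively.
3. State the reference for change.
4. Enter the same hospitalization's pre-exercise and 0 h VAS as covariates. With both in the model and slopes common to all visits, the treatment estimate is the same whichever of the two is the reference.
5. Name the JGT–placebo difference averaged over the listed visits as the primary contrast.

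The cost is wording only, because every score is already scheduled. The changes should be made before unblinding. The downside is that an effect confined to the excluded early hours would not count toward the primary result.
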